#### Plans to give access to the full protocol, participant level-data and statistical code {31c}

No later than 3 years after the collection of the final long term follow-up data collection, a completely anonymized set of participant-level data will be made available, to be shared upon reasonable request. Trial protocol and statistical code will also be made available upon reasonable request.

### Oversight and monitoring

#### Composition of the coordinating center and trial steering committee {5d}

Principal investigator.

Trial planning.

Design and conduct of SWEMMA.

Preparation of protocol and revisions.

Preparation of CRFs.

Organizing TMSC meetings.

Publication of study reports.

Member of Steering Committee.

Trial Management and Steering Committee (TMSC).

(see title page for members).

Trial planning.

Agreement on final protocol.

Organization of TMSC meetings.

All TMSC members will be lead- or sub investigators.

Recruitment of subjects and liaising with coordinating site principal investigator.

Reviewing progress of the trial and if necessary, implementing changes to the protocol to facilitate smooth continuation of the trial.

Advice for lead investigators.

Budget administration.

Agreement on final study report publication.

Data management committee.

Independent of the study organizers.

Management of trial IT systems and data entry.

Responsible for CRF functionality and maintenance.

Responsible for trial master file.

Randomization.

Data verification.

Responsible for performing primary outcome analysis.

Lead investigators.

In each participating center, a lead investigator will be identified (senior neurosurgeon/neurointerventionalist), to be responsible for screening, recruitment, data collection, and completion of relevant CRF entries. Lead investigators will be steering committee members.

#### Composition of the data monitoring committee, its role and reporting structure {21a}

Monitoring duties will be performed by Forum Söder, a Lund University affiliated division of Clinical Studies Sweden, an independent organization funded by the Swedish Research Council. The monitor will perform periodic on-site visits. These visits will be done prior to enrollment of the first subject and at intervals during the study. The investigational site will allow the monitor access to the CRFs and supporting source data (unless prohibited by national law). The monitor may also perform on-site review of medical records if there is a subject death, any unanticipated adverse events, or higher frequency of adverse events than expected. The study monitor is responsible for the conduct and administration of this clinical study. These responsibilities include maintaining regular contact with each investigational site and conducting on-site monitoring visits at each investigational site to ensure compliance with this investigational plan, to verify that accurate and complete data are being submitted in a timely manner, and to verify that the investigative site facilities continue to be adequate. Concerning completed eCRFs for all study patients, the monitor will perform 100% source document verification for all subjects.

Monitoring responsibilities performed by Forum Söder, or its designees include, but are not limited to the following:Site initiation visits.Interim monitoring visits to:**◦** Assess protocol compliance**◦** Conduct source document verification**◦** Assess case report forms accuracy and completeness

Telephone contacts with siteMaintenance of records of investigator/monitor contactsFinal site close-out visit

### Adverse event reporting and harms {22}

#### Adverse events and complications

Throughout the course of the clinical investigation, all adverse events will be recorded on the applicable adverse event form in the eCRF and in the subject’s medical records. In this study, adverse events will be defined and classified per ISO 14155:2020(E) Clinical Investigations of Medical Devices in Human Subjects—Good Clinical Practice and as further described in this protocol. The date of onset, date of resolution, severity, and action taken will be evaluated by the Investigator. The relationship to the device, relationship to the procedure, and clinical significance will be evaluated. The neurological outcomes and adverse events will be reported.

#### Adverse event classification and definitions

An adverse event (AE) is any untoward medical occurrence, unintended disease, or injury, or untoward clinical signs (including abnormal laboratory findings) in subjects, users, or other persons, whether or not related to the medical device (ISO 14155:2011).

Note 1: This definition includes events related to the medical device or the comparator.

Note 2: This definition includes events related to the procedures involved.

Note 3: For users or other persons, this definition is restricted to events related to medical devices.

Disease signs and symptoms that existed prior to study participation are not considered AEs unless the condition recurs after the subject has recovered from pre-existing condition or the condition worsens in intensity or frequency during the study.

A serious adverse event (SAE), as per the European Standard ISO 14155:2020(E), is an AE that led to any of the following:▪ Death▪ Serious deterioration in the health of subject, users or other persons as defined by one or more of the following:

A life-threatening illness or injuryA permanent impairment of a body structure or body function including chronic diseasesIn-patient or prolonged hospitalizationMedical or surgical intervention to prevent life-threatening illness of injuryFetal distress, fetal death, a congenital abnormality, or birth defect including physical or mental impairment

Planned hospitalization for a pre-existing condition, or a procedure required by the protocol, without serious deterioration in health, is not considered a serious adverse event.

#### Adverse event assessments

Relatedness:Procedure-related: Event has a strong temporal relationship to the study procedure. This includes AEs attributable to any device(s) used at procedure, such as access devices, delivery microcatheters, embolic materiel, non-ionic contrast media, guidewires, or any other adjunctive, approved/cleared device for treatment of intracranial vascular pathologyDevice-related: Event has a strong temporal relationship to the use of any other particular device(s)Unknown: Event relationship cannot be attributed to any of the above categories and remains undetermined

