#### Procedure-related adverse events

An adverse event is procedure-related when, in the judgment of the investigator; it is reasonable to believe that the event occurs during the interventional or standard procedure, irrespective of devices used.

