#### Device-related adverse events

An adverse event is device-related when, in the judgment of the investigator, the clinical event has a reasonable time sequence associated with use of any device exclusively used during the interventional procedure and is unlikely to be attributed to concurrent disease or other procedures or medications. It is reasonable to believe that the *device* directly caused or contributed to the adverse event.

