#### Event reporting requirements

Any adverse event that occurs during the study must be recorded and reported using the appropriate adverse event eCRF and recorded in the subject’s medical records.

These will include events occurring from the point of consent until a subject exits the study. The investigator must sign each AE eCRF report. Investigators must obtain all information available to determine the causality and outcome of the AE and to assess whether it meets the criteria for classification as serious and the relationship of each adverse event to the procedure or device. This determines whether it requires notification to the sponsor, regulatory agency, and, as applicable, EC, within the specified reporting timeframe. AEs will be categorized using the definitions in Sects. 18.1–18.5.

Pre-existing medical conditions or symptoms occurring prior to the start of the procedure should not be reported as adverse events. In the situation where there is a worsening of a pre-existing medical condition or symptom due to a study related procedure, an adverse event should be reported.

In the case of any AE, the investigator shall submit to Sponsor a report within 10 working days after the investigator first learns of the event.

The investigator is required to report all SAEs within 24 h after first learning of the event to the sponsor. The primary method of reporting SAEs will be through the eCRFs. If the database is unavailable, the investigator may fax or email in the information. As soon as the database becomes available, the investigator must complete data entry. Depending upon the nature and seriousness of the adverse event, the sponsor may request the investigator to provide anonymous copies of the subject’s available supporting documentation (such as the subject’s laboratory tests, hospital records, discharge reports, autopsy reports, investigator summaries, etc.) to document the adverse event. The sponsor is responsible in Europe for ensuring that the required and adequate information concerning the reported SAE is relayed to the appropriate Ethics Committee and Competent Authority using the MEDDEV 2.7/3 SAE Report Table. All other adverse events (i.e., other than serious adverse events) must be recorded on the appropriate adverse event eCRF.

The sponsor, in cooperation with the Investigator, will assess all serious adverse events for potentially reporting to the Regulatory Authorities and EC.

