#### Data Safety Monitoring Board

The Data Safety Monitoring Board (DSMB) comprises at least 3 non-Investigator clinicians with expertise in interventional neuroradiology/neurosurgery that will review all adverse events occurring in the study according to the DSMB Charter. The DSMB will meet and review all clinical events continuously.

Any event meeting the definition of serious adverse event (SAE) must be adjudicated by the DSMB. The DSMB will also be provided with listings of all events and may choose to adjudicate events that are not serious in nature. Members may discuss any event with the investigator who was involved with the subject in question. The DSMB will use the same rating scale for relatedness. The DSMB adjudicated adverse events will be used in the analysis of the primary safety endpoint; DSMB will review and adjudicate the Medical Monitor’s categorization of event type and severity using the rating system previously referenced.

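### The printed relatedness rules for adverse events conflict, so counts of procedure- and device-related events are ambiguous and not reliably comparable between arms

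*Protocol article*

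**What the plan says.** Adverse event assessments (Protocol article, item 22) sets the relatedness scale. An event is procedure-related if it is closely linked in time to the study procedure, and the text adds: "This includes AEs attributable to any device(s) used at procedure, such as access devices, delivery microcatheters, embolic materiel". Device-related is then kept for devices other than these. The third and last category is "Unknown: Event relationship cannot be attributed to any of the above categories and remains undetermined".

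Two short sections then define the first two categories again. Under Procedure-related adverse events, an event qualifies when, in the investigator's judgment, "it is reasonable to believe that the event occurs during the interventional or standard procedure, irrespective of devices used". Under Device-related adverse events, it qualifies when "the clinical event has a reasonable time sequence associated with use of any device exclusively used during the interventional procedure", with further conditions on causation.

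Adverse event classification and definitions counts events as adverse events "whether or not related to the medical device", and its first note extends this to the comparator.

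The scale is put to use in two places. Event reporting requirements has adverse events categorised by the definitions and says of the investigator's judgment of seriousness and relationship: "This determines whether it requires notification to the sponsor, regulatory agency, and, as applicable, EC, within the specified reporting timeframe". The Data Safety Monitoring Board section states: "The DSMB will use the same rating scale for relatedness".

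**The concern.** One event can receive different codes depending on which section the investigator reads, and both codes would follow the protocol. Treatment allocation is open, so the investigator judges relatedness knowing the arm. Unclear definitions, one of them tied to a single arm, are most exposed to differential use in that setting.

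Three things are at stake: any table of procedure- or device-related events by arm, the meaning of the board's relatedness adjudication, and the part of notification that depends on relatedness. The Discussion makes comparable complication rates part of the case for embolization, so readers are likely to want harms broken down by cause.

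**Working it through.** The plan gives no figure to reproduce here. The check takes typical events and classifies each one under the list (Adverse event assessments) and under the later definitions (Procedure-related adverse events; Device-related adverse events).

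1. **Event caused by embolic material or a microcatheter.**
   - List: procedure-related, because these items are named there. It is not device-related, because that category is left for other devices.
   - Later device definition: these are devices "associated with use of any device exclusively used during the interventional procedure", so the event is device-related if the causation conditions are met.
   - Result: contradiction.

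2. **Complication that appears after the procedure has ended.** The protocol's own times show how narrow the later procedure definition is. Intervention description estimates 30 min to 1 h from incision to closure for surgery, and about 1–2 h from vascular access to closure for embolization. The surgical drain stays for 24 h and staples for 7–14 days.
   - List: a drain event at 20 h, a wound infection found at staple removal or an access-site complication next day can qualify through its link in time to the procedure.
   - Later procedure definition: none of the three happens during a procedure lasting at most 1 h or 2 h, so none qualifies.
   - Result: contradiction, in both arms.

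3. **Device event in the surgical arm, for example from the drain catheter.**
   - List: its device category names no arm and does not exclude such an event, although the devices it names are endovascular.
   - Later device definition: the procedure-related section sets the interventional procedure apart from the standard one. A device exclusive to the interventional procedure is therefore an embolization device, and the drain event cannot qualify.
   - Result: an asymmetry between arms, found in the later device definition only, although the adverse event definition covers the comparator.

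4. **Clearly unrelated event, for example pneumonia at month 8.** It is an adverse event by definition and is recorded, because reporting runs from consent to study exit.
   - List: it is neither procedure- nor device-related. The third category requires an undetermined relationship, and this one has been determined.
   - Result: strictly, no category fits. If the event is filed under the third one, it cannot be told apart from a truly unresolved event.

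5. **Does any pre-specified outcome depend on these labels?** The safety objective, secondary outcome V and the secondary analysis of the all-complications rate cover complications, adverse events and serious adverse events by number and severity. None is filtered by relatedness.
   - Result: the overall comparison between arms is unaffected.

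**The case against.** The strongest reply is that little depends on relatedness.

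- **Outcomes.** A reader might infer that procedural harm cannot be compared between arms at all, or that delayed surgical complications are lost. The document supports neither. Outcome V counts every event, the later procedure definition covers both procedures, and being outside it changes a label, not whether the event is recorded. No between-arm analysis of related events is stated, so there is no planned estimate to call biased. This part of the reply stands.
- **Reporting.** Every adverse event goes to the sponsor within 10 working days and every serious one within 24 h, whatever its relatedness. The sponsor assesses all serious events for onward reporting, and all deaths go to the ethics committee and competent authority. The board adjudicates every serious event and sees listings of all events. This confines the exposure to onward notification. The board's check does not remove the ambiguity, because it uses the same scale.
- **Arm restriction.** It would be too strong to say that the protocol recognises device events only in the embolization arm. That holds for one of the two device definitions. Limiting device-relatedness to the tested treatment could be deliberate, but then the two definitions should agree.
- **Missing level.** The article classifies events by ISO 14155 and by its own further description, and it points to section numbers that do not appear in it. The full protocol or eCRF may hold a level for unrelated events, so this limb is limited to the scale as shown. The contradictions are different in kind: they lie in printed text, and the ISO reference does not resolve them.

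**Conclusion.** The concern holds in a limited form. The printed definitions are incompatible on embolization devices and on delayed complications, they differ on device events in the surgical arm, and the scale as shown has no level for unrelated events. Counts of procedure- and device-related events, the board's relatedness adjudication and relatedness-dependent onward notification are therefore ambiguous and not reliably comparable between arms. The comparison of all complications, adverse events and serious adverse events stands.

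No size can be put on the misclassification. The protocol gives neither complication rates by arm nor the share appearing after the procedure, and any count would only reflect assumed rates. The conclusion rests on reading the interventional procedure as embolization, which the contrast with the standard procedure supports, and on the printed article being the text that investigators and the board apply. The point should be fixed because the remedy is cheap, but it does not threaten a pre-specified outcome.

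**What to change.** Replace the three sections with one set of definitions, worded and applied identically in both arms.

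- Score relationship to the procedure and relationship to the device as two separate items. The Adverse events and complications section already asks for both to be evaluated.
- Give each item an explicit level for unrelated events, distinct from undetermined. The number of intermediate grades is the sponsor's choice.
- Remove the requirement that the event happen during the procedure, so that delayed complications of either procedure can qualify.
- Remove the restriction to devices exclusive to the interventional procedure, so that device events in either arm can qualify, and state how an event from a device used in the procedure is scored on each item.
- Have the board use the reconciled scale, and re-code events already recorded. Recruitment began in March 2022, so some may exist.

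The cost is a protocol amendment with the approvals that the amendments section requires, an eCRF field change, and modest re-coding with repeat adjudication of the serious events affected. No outcome, sample size or planned test changes.

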#### Procedure-related adverse events

An adverse event is procedure-related when, in the judgment of the investigator; it is reasonable to believe that the event occurs during the interventional or standard procedure, irrespective of devices used.

#### Device-related adverse events

An adverse event is device-related when, in the judgment of the investigator, the clinical event has a reasonable time sequence associated with use of any device exclusively used during the interventional procedure and is unlikely to be attributed to concurrent disease or other procedures or medications. It is reasonable to believe that the *device* directly caused or contributed to the adverse event.

#### Event reporting requirements

Any adverse event that occurs during the study must be recorded and reported using the appropriate adverse event eCRF and recorded in the subject’s medical records.

These will include events occurring from the point of consent until a subject exits the study. The investigator must sign each AE eCRF report. Investigators must obtain all information available to determine the causality and outcome of the AE and to assess whether it meets the criteria for classification as serious and the relationship of each adverse event to the procedure or device. This determines whether it requires notification to the sponsor, regulatory agency, and, as applicable, EC, within the specified reporting timeframe. AEs will be categorized using the definitions in Sects. 18.1–18.5.

Pre-existing medical conditions or symptoms occurring prior to the start of the procedure should not be reported as adverse events. In the situation where there is a worsening of a pre-existing medical condition or symptom due to a study related procedure, an adverse event should be reported.

In the case of any AE, the investigator shall submit to Sponsor a report within 10 working days after the investigator first learns of the event.

The investigator is required to report all SAEs within 24 h after first learning of the event to the sponsor. The primary method of reporting SAEs will be through the eCRFs. If the database is unavailable, the investigator may fax or email in the information. As soon as the database becomes available, the investigator must complete data entry. Depending upon the nature and seriousness of the adverse event, the sponsor may request the investigator to provide anonymous copies of the subject’s available supporting documentation (such as the subject’s laboratory tests, hospital records, discharge reports, autopsy reports, investigator summaries, etc.) to document the adverse event. The sponsor is responsible in Europe for ensuring that the required and adequate information concerning the reported SAE is relayed to the appropriate Ethics Committee and Competent Authority using the MEDDEV 2.7/3 SAE Report Table. All other adverse events (i.e., other than serious adverse events) must be recorded on the appropriate adverse event eCRF.

The sponsor, in cooperation with the Investigator, will assess all serious adverse events for potentially reporting to the Regulatory Authorities and EC.

For any adverse event that is ongoing at the time of the initial report, periodic follow-up information is required until the adverse event is resolved or is judged to be chronically stable or until the conclusion of the study for the subject. The site should submit relevant follow-up information related to the adverse event as soon as it is available.

#### Subject death

Subject death during the investigation must be reported via eCRF within 24 h of investigator’s knowledge of the death. Notification of death must include a brief statement of the relevant details of the death and is required to be signed by the Investigator. In addition, all patient deaths must be reported to the specific Ethics Committee and Competent Authority in accordance with regulatory requirements. The method of declaration will conform to the current regulations. A copy of the death records, death certificates, and an autopsy report (if performed) are required to be sent to sponsor or designee, within ten [10] days following the death.

In the event of subject death, efforts should be made to perform an autopsy. For subjects that do not undergo autopsy, written documentation from the investigator will be required providing justification as to why an autopsy was not performed.

